## Abstract

**Background:**

The TAPS Tool (“Tobacco, Alcohol, Prescription drug, and illicit Substance use”) is a screening and brief assessment for detecting unhealthy substance use in healthcare settings that was developed by the National Institute on Drug Abuse Clinical Trials Network and validated in a multisite study. Our team developed a Spanish language version of the TAPS Tool that supports provider- and self-administration screening using a mobile/web-based platform, the TAPS Electronic Spanish Platform (TAPS-ESP).

**Methods:**

This article describes the protocol and rationale for a study to validate the TAPS-ESP in a sample of Spanish-speaking primary care patients recruited from a network of community-based clinics in Texas (target *N* = 1,000). The TAPS-ESP will be validated against established substance use disorder diagnostic measures, alternative screening tools, and substance use biomarkers. The study will subsequently examine barriers and facilitators to screening with the TAPS-ESP from a provider workflow perspective using qualitative interviews with providers.

**Discussion:**

Validating a Spanish language version of the TAPS Tool could expand access to evidence-based, linguistically accurate, and culturally relevant substance use screening and brief assessment for an underserved health disparity population.

*Trial registration***:** The study was registered with www.clinicaltrials.gov: NCT05476588, 07/22/2022.

## Background

Substance Use Disorders (SUDs) for tobacco, alcohol, illicit drugs, and non-medical use of prescription drugs contribute to substantial public health and social problems, and minority populations bear a great share of the disease burden [1–7]. Substance use can have major consequences for health, including overdose death, intoxication-related injury, and soft tissue infections from drug injection. SUDs can exert considerable public health burden in morbidity and mortality related to their long-term sequelae (e.g., cirrhosis from alcohol, lung and esophageal cancers from tobacco, hepatitis C infection from injection drug use). However, significant health consequences of unhealthy substance use can manifest even with less severe and sub-diagnostic SUDs.

For these reasons, the US Preventive Services Task Force now recommends that all adults receive routine screening for all substances as part of primary care. While screening for tobacco and alcohol have long been recommended on the basis of rigorous evidence synthesis from randomized trials [8–10], the Task Force recently updated its position to recommend screening for illicit drugs and non-medical prescription drug misuse [11]. This change was prompted by a growing body of research demonstrating the ability of brief screening tools to validly detect unhealthy substance use in large, methodologically rigorous studies. The US Surgeon General has strongly endorsed implementing substance use screening and intervention in health care systems [12].

Even with the well-described comorbidities of SUD with serious medical and mental health conditions [13], many primary care settings fail to systematically screen for unhealthy substance use, or do not use best evidence screening tools [14]. However, recent research has yielded more empirically-validated screening tools to detect substance use problems in primary care [15–18]. Although substance use problems are prevalent in primary care populations, most individuals who access primary care do not seek treatment in the behavioral health service system on their own [19].

Limited English Proficiency is a barrier to quality behavioral health care. Demographic changes in populations served by the large nationwide network of Federally Qualified Health Centers (FQHCs) show a rise in substance use by young, low-income, racial and ethnic minorities, especially Hispanic Americans [20]. Individuals with limited English proficiency are less likely to self-identify a need for behavioral health services, resulting in a longer duration of untreated disorders [21]. Accurate screening, diagnosis, and treatment are entirely dependent on a linguistically-accurate and culturally-appropriate identification and assessment, especially for sensitive topics such as substance use. Language accessibility is essential to the treatment of mental and physical health disorders [22], the lack of which is a significant contributor to health disparities, lack of patient satisfaction in healthcare, and poor quality patient education and understanding of their disorder [23, 24]. Health disparities among racial minorities are amplified in the presence of comorbid substance use and psychiatric disorders [25, 26]. Despite the clear need, few substance use screening tools have been validated with Spanish-speaking populations.

There are over 60 million Hispanics in the US, comprising 18.5% of the population, making it the largest and fastest growing minority group [27]. Three-in-four (73%) Hispanics speak Spanish at home, and nearly 40% are Spanish dominant (or Spanish preferred), making it the most spoken non-English language in the US [28]. Limited English proficiency, limited health literacy, geographic inaccessibility, and lack of medical insurance are all more common among immigrant minority groups of low socio-economic status [29].

National epidemiological survey data shows that, among Hispanics in the US, rates of past year substance use were 19.8% for tobacco, 57.9% for alcohol use, 13.5% for cannabis, and 8.2% for illicit drug use for non-medical use of prescription drugs [30]. While these rates are similar to those of the general population, Hispanics are significantly less likely than non-Hispanics to access substance use treatment when they need it and are less likely to perceive a need for it despite meeting standard clinical thresholds for substance use problems [31]. Thus, Hispanics experience disparities in the identification of SUDs and in access to care. Hispanics experience a disproportionate burden of disability associated with mental health disorders because of these disparities [32, 33].

The past decade has increased emphasis on the role of technologies in patient assessment and care, with health systems adopting electronic health records (EHRs) and other health information technologies [34]. More recently, the COVID-19 pandemic has led to a rapid adoption of health communication technologies, with many primary care providers quickly building upon their telehealth infrastructure to deliver more services remotely. Valid screening and diagnostic technologies that can be integrated into EHR systems have great potential for improving patient care and reducing health disparities, both for services provided in-clinic and remotely.

Although a number of substance use screening tools are available, many have shortcomings that may make them unsuitable for the modern primary care environment. Some long-established screeners like the CAGE for alcohol or the Fagerstrom Test for Nicotine Dependence focus narrowly on a single substance. Other tools (e.g., the Drug Abuse Screening Test, or DAST) do not differentiate between types of substances. Others like the World Health Organization’s ASSIST have been criticized as being too long. The need for a single, brief instrument without these shortcomings drove the National Institute on Drug Abuse Clinical Trials Network (NIDA-CTN) to develop the “Tobacco, Alcohol, Prescription medication, and illicit Substance use screening Tool” (or TAPS Tool) [16, 18, 35, 36]. The TAPS Tool is a two-stage screening and brief assessment instrument based on the WHO ASSIST-Lite [37] that first screens the four broad substance use categories (tobacco, alcohol, prescription drug misuse, and illicit substances), then branches to the brief assessment in which the patient is assessed for more specific risks related to an expanded array of substances (tobacco, alcohol, cannabis, cocaine, methamphetamines, prescription stimulants, heroin, prescription opioids, sedatives, and other substances). The 4-item screener triggers brief assessment on these substance categories, and each substance yields a score of 0–3 (except alcohol, which is scored on a 0–4 range), which conveys to providers whether an intervention is indicated (a score of 1 suggests sub-diagnostic problem use; a score of 2 suggests substance use disorder). The TAPS Tool was validated against established diagnostic assessments in interviewer- and self-administered formats in a large, multi-site study [16]. However, the original TAPS study was only conducted using an English language version. Only 11.7% of the sample reported Hispanic ethnicity, and the ability to speak and read English was an inclusion criterion.

There has been surprisingly little existing research within the US that has validated substance use screening in Spanish. Saitz et al. examined Spanish-language versions of the CAGE and AUDIT alcohol screeners in a primary care practice among 210 Hispanic patients [38]. Over 1 in 3 participants met criteria for alcohol use disorder, defined at the time as alcohol abuse or dependence under the Diagnostic and Statistical Manual of Mental Disorders, 4^th^ edition (DSM-IV). The widely used AUDIT proved unsuitable for this sample, with a detection sensitivity of only 51% for alcohol use disorder, while the CAGE showed good sensitivity and specificity for these diagnoses (80% and 93% at a cut-point of 2, respectively).

Bedregal et al. studied test–retest reliability of Spanish-language translations of the Drug Abuse Screening Test-10 (DAST-10) and Reduced/Annoyed/Guilty/Start (RAGS) screeners [39]. Of 222 Hispanic participants recruited, 78 completed both interviews. The measures were administrated in counterbalanced order. Both screens were found to have unidimensionality and were able to differentiate between participants with drug vs. alcohol vs. no substance use problems [39]. McCabe et al. examined the factor structure of a Spanish-language version of the College Alcohol Problems Scale in a sample of 125 Spanish-speaking undergraduates [40]. The researchers found acceptable fit for a two-factor model and acceptable internal consistency (α = 0.76 and 0.73 for the personal and social problems subscales, respectively). However, this scale is considered to be more of a research measure for problematic alcohol use in college students, and not suitable for general screening in primary care [40].

In a recent study conducted in the US and Spain, researchers used item response theory to construct an English and Spanish version of a computerized adaptive substance use scale (the CAT-SUD), with Spanish-speaking participants drawn from both countries [41]. The calibration and validation study found 11 items that had high correlation with the full 168-item scale (r = 0.91) and able to identify SUDs (AUC = 0.85). Like most other validation studies, this study used the Spanish-language translation of the Composite International Diagnostic Interview (CIDI) SUD items as the diagnostic standard [41]. The prior research on Spanish-language validation of substance use screening tools in the US has shown promising reliability and validity. However, this literature is characterized by small samples, has focused on a limited number of substances, and has mostly been fielded in non-primary care populations. The current study builds on this prior literature with a validation study.

Our team previously developed a Spanish-language version of the TAPS Tool and designed a technology platform to deliver the screening and brief assessment to a Spanish-speaking, health disparity population in community health centers. We refer to the resulting package as the TAPS-Electronic Spanish Platform (TAPS-ESP), which includes resources for both traditional interviewer-administered and electronic self-administered formats. Findings from our small feasibility, acceptability, and preliminary validation study of TAPS-ESP support the utility of the TAPS Tool, which yielded similar rates of detection of substance use as Spanish-language versions of well-established, widely used measures. Moreover, participants reported high acceptability of the TAPS Tool, which is consistent with the findings of the English language multisite validation study [42]. Since Hispanics with SUDs significantly underutilize specialty treatment due to barriers stemming from stigma, lack of social support, cultural factors, and family conflict [43–45], the next stage for this type of research is to conduct a full validation of the TAPS-ESP in a large sample to build its evidence base for Spanish-speaking primary care patients.

## Methods

### Overview

This study will validate the TAPS-ESP in both interviewer- and self-administered formats, largely mirroring the methodology of the seminal English language validation study.

This project is motivated and informed by the principles of the Conceptual Framework for Advancing Health Disparities Research within the Health Care System described by Kilbourne et al. [46]. Briefly, this framework posits a nested structure of factors that perpetuate health disparities within the health services arena, including healthcare system factors (organization, financing, culture, etc.), within which patient and provider factors intersect at the clinical encounter. It is at this level that patient-provider communication and cultural competence are paramount. The availability of linguistically-accurate screening and brief assessment resources (especially if paired with clinical decision support) has the potential to improve provider competency in addressing substance use problems, while elevating patients’ receptivity to provider communication about behavior change, harm reduction, or referral. The framework further organizes disparities-focused services research into phases of (a) detection (identifying, measuring, and tracking disease in a defined population), (b) understanding (determinants and perpetuators of disparate service access and outcomes, including at the level of patients, the clinical encounter, and the health care system), and (c) reduction (translation and dissemination of evidence-based practices and policies). The TAPS-ESP project is focused on the detection phase but will also target the understanding phase by considering acceptability of the TAPS-ESP among clinic patients and perceived barriers and facilitators to its use by providers. In a broad sense, the TAPS-ESP effort seeks to directly address gaps in access to evidence-based substance use screening for a health disparity population by removing linguistic barriers and developing the evidence base with the target population.

### Setting and recruitment

The TAPS-ESP validation study will be conducted at Baylor Scott and White Health (BSWH), the largest non-profit health system in Texas and one of the largest in the US. The BSWH system includes multiple primary care sites across the Dallas/Ft. Worth metroplex. Participants will be recruited from up to seven primary care sites of the Community Clinic network operated by BSWH. Depending on the clinic site, Hispanic patients make up 51%-80% of the patient population, and the majority are Spanish-dominant or Spanish-preferred. All research staff will be bilingual, native Spanish speakers. The providers in the clinic will deliver care in Spanish, some as native Spanish speakers, some with interpreters present.

We will use a multi-pronged recruitment strategy, including (a) direct invitations by research staff in the clinic waiting room, (b) direct invitations from telehealth visit schedules, (c) direct provider referrals, and (d) patient-initiated contact from advertisements posted in the clinic sites. Within these approaches, we will focus recruitment on the general primary care population, as well as targeting patients who are engaged with the behavioral health services provided within BSWH (where prevalence of substance use is likely to be higher).

*Inclusion criteria* will be: (1) age 18 or older; (2) BSWH patient; and (3) Spanish-language preferred (with the ability to read Spanish).

*Exclusion criteria* will be: (1) unable to provide informed consent (e.g., due to impairment or psychosis). All research activities (e.g., informed consent discussion and interview) will occur in Spanish. Participants will sign an IRB-approved Spanish language consent form.

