#### Analyses of TAPS-ESP performance

The TAPS-ESP scores will be validated against the CIDI as the primary diagnostic reference standard. Secondary screeners and assessments will be similarly examined from the standpoint of concurrent validity. Statistical analysis of TAPS-ESP screening test performance will employ a receiver operating characteristics (ROC) approach, including appraisal of sensitivity, specificity, positive predictive value (PPV), negative predictive value (NPV), and area under the curve (AUC). Optimal score cut-points will be confirmed using the *Youden’s J* statistic (unweighted and weighted prioritize sensitivity). Our target sensitivity and specificity will follow the established standards in screening test research, where test performance is considered acceptable, good, and excellent, at value thresholds of 0.7, 0.8, and 0.9, respectively. In addition, we will use the concordance correlation coefficient (CCC) [55], similar to a weighted κ statistic, to compare the agreement, accuracy, and precision associated with the screening success of the TAPS-ESP. For detecting the CIDI-derived DSM-5 substance use disorder diagnosis, we will examine TAPS-ESP cut-points for the 4-item screener as well as the brief assessment component in detecting levels of problem severity defined on the basis of DSM-5 criteria. As done in the original TAPS study, we will examine cut-points for detecting three different tiers of unhealthy substance use: Problem use (1 + criterion), SUD (2 + criteria), and moderate-to-severe SUD (4–11 criteria). Detection of SUD at any level will be the primary outcome of interest for each substance category. We will also examine performance of the TAPS-ESP in eliciting disclosure of substance use, irrespective of endorsing SUD-related problems.

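### If behavioral-health patients are over-recruited, pooled PPV and NPV will describe the recruitment mix rather than general primary care

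*Protocol article*

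**What the plan says.** Under Setting and recruitment, the article directs recruitment at general primary care and adds a second aim, "targeting patients who are engaged with the behavioral health services provided within BSWH (where prevalence of substance use is likely to be higher"). No quota, cap or expected share is given for either group. The same section lists four contact routes, one of them provider referral.

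Under Analyses of TAPS-ESP performance, the ROC approach is described as "including appraisal of sensitivity, specificity, positive predictive value (PPV), negative predictive value (NPV), and area under the curve (AUC"). Detection of SUD at any level is the primary outcome for each substance. The next section, on comparisons, names administration format, sex and age as the breakdowns; recruitment stream is not among them. Nothing in the article restricts predictive values to one stream, reweights them, or restates them at a reference prevalence.

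The population of interest is clear. The Abstract sets out to "validate the TAPS-ESP in a sample of Spanish-speaking primary care patients", and the Background gives the aim as to "build its evidence base for Spanish-speaking primary care patients".

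**The concern.** Sensitivity and specificity are conditional on true status, so choosing a higher-prevalence sample does not by itself change them. PPV and NPV are conditional on the test result and change with prevalence even when the test behaves identically. A plan that deliberately seeks a higher-prevalence group, pools it with general primary care and then reports PPV gives a number that depends partly on how recruitment went.

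Clinicians are likely to read a published PPV as the chance that a screen-positive primary care patient has an SUD. If the sample is enriched, that reading is too optimistic and invites more confidence in a positive screen than is justified. Without results by stream, no reader could tell how much of the figure comes from the mix. The Background also criticises earlier validation work for being done mostly outside primary care, so keeping the general stream identifiable matters to the article's own argument.

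**Working it through.** **The plan's own figure.** The article states no PPV or NPV. Its related figure is Table 2, which reproduces. For an exact binomial test of H0 = 0.50 with 0.025 in each tail:

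- H1 = 0.70: the smallest n with power of at least 0.80 is 49 (reject at 32 or more; tail probability 0.0222; power 0.810). 49 / 0.05 = 980.
- H1 = 0.80: the smallest n is 20 (reject at 15 or more; tail probability 0.0207; power 0.804). 20 / 0.05 = 400.

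The other rows follow in the same way. The sample size for sensitivity is not at issue here.

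**Inputs for the predictive values**

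- Prevalence p: 2.5%, 5%, 10% and 20% (Table 2). The sample size rests on 5%.
- Sensitivity (Se) 0.80 and specificity (Sp) 0.90: assumed, chosen from the article's thresholds of 0.7, 0.8 and 0.9.

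**Formulas**

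PPV = Se·p / [Se·p + (1 − Sp)(1 − p)]

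NPV = Sp(1 − p) / [Sp(1 − p) + (1 − Se)p]

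At 5%: PPV = 0.040 / (0.040 + 0.095) = 0.296; NPV = 0.855 / (0.855 + 0.010) = 0.988.

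At 10%: PPV = 0.080 / (0.080 + 0.090) = 0.471; NPV = 0.810 / (0.810 + 0.020) = 0.976.

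| Prevalence | PPV | NPV |
|---|---|---|
| 2.5% | 0.170 | 0.994 |
| 5% | 0.296 | 0.988 |
| 10% | 0.471 | 0.976 |
| 20% | 0.667 | 0.947 |

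The pattern does not depend on this choice of Se and Sp. Going from 5% to 10%, PPV moves from 0.109 to 0.206 when both are 0.70, from 0.174 to 0.308 when both are 0.80, and from 0.321 to 0.500 when both are 0.90.

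**What mix would produce such a shift.** Assume 5% prevalence in the general stream and 20% in the behavioral-health stream; neither figure by stream is in the article. With behavioral-health share w, pooled p = 0.05(1 − w) + 0.20w. At Se 0.80 and Sp 0.90:

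| Share w | Pooled p | PPV | NPV |
|---|---|---|---|
| 0 | 5.0% | 0.296 | 0.988 |
| 10% | 6.5% | 0.357 | 0.985 |
| 20% | 8.0% | 0.410 | 0.981 |
| 30% | 9.5% | 0.456 | 0.977 |
| 50% | 12.5% | 0.533 | 0.969 |

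Reaching 10% needs w = (0.10 − 0.05) / 0.15 = one third.

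If behavioral-health patients are themselves part of the screening population, only the excess over their natural share matters. With an assumed natural share of 20% and a recruited share of 30%, PPV goes from 0.410 to 0.456, about 5 points. If the two shares are equal, there is no shift.

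**The case against.** The strongest reply is that this is a condensed article. It says predictive values will be appraised; it does not say they will be one pooled figure offered as the primary care value, and a separate analysis plan may standardise them. That limits the point but does not remove it. The article itself chooses the targeting, the measures and the breakdowns, and as written the combination leaves predictive values tied to the mix.

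Further replies stand. Enrichment is a legitimate way to find enough cases for estimating sensitivity. The targets and the power calculation concern sensitivity and specificity, so predictive values are not the main result. A reader given sensitivity and specificity can work out PPV for a local prevalence. The article's remark about higher prevalence concerns substance use, whereas the primary outcome is SUD; that SUD is also more frequent in this group is likely but not stated.

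Three stronger readings are tempting and are not supported:

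- That pooled PPV is bound to be inflated. No share is given, and behavioral-health patients may enter near their natural share.
- That provider referral is also deliberate enrichment. The article lists "c) direct provider referrals" only as a contact route.
- That sensitivity will be inflated because behavioral-health cases are more severe. Such a spectrum effect is plausible, but nothing in the article shows it.

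**Conclusion.** The point holds in a conditional form. The plan seeks a higher-prevalence group, reports prevalence-dependent measures and names no breakdown by recruitment stream. If that group exceeds its natural share of attendance, pooled PPV is likely to be too high and NPV slightly too low for general primary care.

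The direction assumes higher SUD prevalence in the targeted group and similar sensitivity and specificity in both streams. The size is unknown. A move from 5% to 10% prevalence would add about 17 points to PPV (0.471 − 0.296) and take about 1 point from NPV (0.988 − 0.976) at Se 0.80 and Sp 0.90, but nothing in the article shows that a shift of that size will occur. The sample size and the primary assessment of sensitivity are not called into question by this point. It is worth correcting because the change is cheap and PPV is easily misread.

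**What to change.** Keep the recruitment strategy and change the reporting:

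1. Record each participant's recruitment stream (general primary care or targeted behavioral health). Recruitment was still under way when the article was written. For those already enrolled, recover the stream from recruitment records where possible.
2. Report sensitivity and specificity by stream.
3. Report PPV and NPV for the general primary care stream, and also by Bayes' rule at 2.5%, 5%, 10% and 20%. Use general-stream sensitivity and specificity in that calculation if they differ materially between streams, since pooled values would carry any spectrum effect forward.
4. If pooled PPV and NPV are shown, label them as describing the study sample only.

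The cost is one variable and one table, with no extra participants. The downside is precision. Under the illustrative mix above with N = 1000 and a 30% behavioral-health share, the general stream would hold 700 × 0.05 = 35 cases, against 35 + 300 × 0.20 = 95 in the pool. At sensitivity 0.80 the standard error is √(0.16/35) = 0.068 rather than √(0.16/95) = 0.041. The comparison between streams would therefore be imprecise for less common substances and should be read as a check, not a test.
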